### 5.3. Other analyses at median 15-years follow-up

The approach to the primary analysis will be adapted to the analysis of secondary outcome events, i.e. definite, probable or possible prostate cancer mortality; all-cause mortality; and metastatic cancer.

For patient reported outcomes (see Section 2.9.2) summary statistics by allocated group will be presented graphically for the baseline, 6-month, 12-month and subsequent assessment points up to 12 years (**we will accept questionnaires returned by September 30th 2021**, by which time all men will have this duration of follow-up). This approach will also be taken for those questionnaires dropped from the battery in November 2018, with the consequent loss of responses for later assessment points being made clear. All graphical presentations will present the full 12 years follow-up but will focus on the novel data for the period from 73 to 132 months.

Analyses will employ multi-level models for repeated measures to estimate average treatment effects. These analyses will be adjusted for the stratification (centre) and minimisation (baseline age, Gleason score, PSA level) variables as described in the previous section. Consistent with the focus of the current analysis, the null

hypothesis of no difference in the population means of an outcome measure between allocated treatment groups, for the period from 73 to 144 months, will be tested.

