### 13.5 Data Collection at The Diagnostic Phase (CC)

The research nurse completes onto the study computer at the earliest opportunity the clinical stage and grade of the disease, including Gleason scores, and whether other tests have been performed, e.g. bone scans or additional PSA tests. It is possible that there will be several appointments or events and results e.g. bone scans during the diagnostic phase, and data collection must occur at each appointment or event on all men with a raised PSA.

Participants are asked to complete questionnaire (Questionnaire MTQ2) containing similar measures used in the PCC clinic questionnaire (MTQ1) with the addition of the UCLA **EPIC** prostate cancer index. The questionnaire will be entered by Bristol. The questionnaire should be completed for each biopsy undertaken, including second or third biopsies.

If localised prostate cancer is diagnosed and the participant is excluded for any reason e.g. for health grounds, then this must be fully documented.

All men unable to proceed to the eligibility appointment for whatever reason should have their ProtecT study data returned to Bristol for data entry and storage, i.e. PCC schedule, MTQ1 and MTQ2 questionnaires, Consent 3, Consent 3.1, eligibility proforma grouped inside PCC schedule and recorded on the front of the schedule.

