### **Description of Statistical Methods (2018 to March 2027)**

The statistical analysis of primary and secondary outcomes conducted for the median 10-year follow-up will be repeated for the median 15-year and 20 year follow-up. In brief, the primary outcome of deaths due to prostate cancer or its treatment will be compared among the three assigned treatment groups on an intention-to-treat basis with the use of Cox proportional hazards regression adjusted for trial centre, age at baseline, Gleason score, and PSA level at baseline (log-transformed). The results of a cumulative incidence

approach, which will avoid bias due to other causes of death, will also be presented (although there was no evidence of such bias in the primary 10-year analysis). This approach will be adapted as necessary for secondary event-based outcomes, e.g. date of disease progression, date of diagnosis of metastatic disease, and all-cause mortality. The previously specified sub-group analyses will be conducted, investigating whether the relative treatment effects vary by age, clinical stage, Gleason score, and PSA level at diagnosis. Patient reported outcomes completed during the complete 11-year follow-up will be compared among the three assigned treatment groups on an intention-to-treat basis. Two-level random-effects models will be used to accommodate the correlation between the repeated assessments for each man. Two-level linear models will be used for continuous measures, and two-level logistic models were used for binary measures. All models will include trial centre, age at baseline, Gleason score, and PSA level at baseline (log-transformed) as covariates. All men with at least one post-randomisation measure available will be included in an analysis; there are no plans to impute missing assessments, although the possible effect of these on the observed results will be investigated through sensitivity analyses.

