| 
Changes to Protocol version 2.4, July 1st 2009
 
 
• New methods of communication were introduced to follow-up non-responders to outcome questionnaires, with additional contact details collected (Section 20.6, p32 of final protocol).
 
• Addition of the EORTC QLQ-C30 questionnaire at 2 and 5 years' follow-up (section 22.2, p34 of final protocol).
 
• Clarification that follow-up starts from the date of randomisation (section 20.4, p31 of the final protocol).
 
• Improved wording to clarify primary outcome as prostate cancer-specific mortality at 10 years' median follow-up (section 22, p33 of final protocol).
 
                                                                                                                                                                                                                                                                                                                                                                                                                                                                                                                                                                                                                                                 |

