## 6.3. Secondary analyses

The approach to the primary analysis will be adapted to the analysis of secondary outcome events, i.e. definite, probable or possible prostate cancer mortality; all-cause mortality; and metastatic cancer (Table 4).

Patient reported outcomes (see Section 2.10.2) by allocated groups (i.e. following the ITT principle) will be presented in a separate companion paper. Summary statistics by group will be presented graphically for the baseline, 6 month, 12 month and subsequent assessment points. Analyses will employ multi-level models for repeated measures to estimate average treatment effects. Random intercepts and random slopes models will be considered. These analyses will be adjusted for the stratification (centre) and minimisation (baseline age, Gleason score, PSA level) variables as described in the previous section, and the baseline measure of the patient reported outcome being considered. The exact nature of formal testing of differences between groups depends upon the trends observed over time in each; in selecting an analysis, the principles of the primary analysis will be followed as closely as possible, and the most parsimonious set of parameters chosen to describe the differences between groups over time.

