## 1. INTRODUCTION & PURPOSE

*This document details the statistical analysis proposed and the presentation that will be followed, as closely as possible, when analysing and reporting the median **15-year** results from the **Prostate Testing for Cancer and Treatment ( ProtecT ) Study**. As far as possible this plan will follow the approaches in the main ProtecT statistical analysis plan written for the primary analysis of median 10-year follow-up, which is available at: <https://njl-admin.nihr.ac.uk/document/download/2021093>*

The purpose of the plan is to:

1. Make explicit the details of the planned analysis, as agreed with the Trial Steering Committee.
2. Ensure that the analysis is appropriate for the aims of the trial, reflects good statistical practice, and that interpretation of *a priori* and post-hoc analyses is appropriate.
3. Explain in detail how the data will be handled and analysed to enable others to perform the actual analysis in the event of sickness or other absence, or to replicate the analyses

Additional exploratory or auxiliary analyses of data not specified in the protocol are permitted but fall outside the scope of this analysis plan (although such analyses would be expected to follow Good Statistical Practice).

The analysis strategy will be made available if required by journal editors or referees when the main papers are submitted for publication. Additional analyses suggested by reviewers or editors will, if considered appropriate, be performed in accordance with the Analysis Plan, but if reported the source of such a post-hoc analysis will be declared.

Amendments to the statistical analysis plan will be described and justified in the final report of the trial.

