### 2.9.2. Secondary outcomes

*Secondary clinical and patient-reported outcomes to be presented in the 15-year results papers are:*

- *overall mortality*

- *metastatic disease*
- *clinical disease progression*
- *initiation of long-term hormone therapy*
- *patient reported outcomes (PROMs)*

*Metastatic disease is defined as positive imaging showing bony, visceral and/or lymph node metastases, or PSA above 100; or bone marrow infiltration with associated systemic symptoms.*

*Clinical disease progression will be measured as person-years free of the consequences of disease progression. Signs of disease progression will include evidence of metastatic disease; the initiation of long-term hormone therapy; diagnosis of clinical T3 or T4 disease; or ureteric obstruction, rectal fistula, or the need for a permanent catheter when these are not considered to be a complication of treatment. There will be a review of cases where disease progression or metastatic disease are uncertain.*

As the ascertainment of clinical disease progression may differ between the three study arms, we will also present the initiation of long-term hormone therapy, to indicate those men whose disease is no longer curable.

The reporting of metastatic disease, clinical disease progression, and initiation of long-term hormone therapy is conditional on securing the data.

*The patient-reported outcomes which have been measured are listed in the Appendix. These measures are derived from validated questionnaires and have been completed at recruitment, at first biopsy, six months after randomisation, and yearly thereafter. These measures will be reported in a separate companion paper, to be submitted for publication at the same time as the primary outcomes paper.*

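### The 15-year PROM models leave out the baseline value of the PROM, which costs precision, although it was collected for most instruments

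*Supplement*

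**What the plan says.** Two current texts set the covariates for the PROM models.

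- 15-year SAP, section 5.3: "These analyses will be adjusted for the stratification (centre) and minimisation (baseline age, Gleason score, PSA level) variables as described in the previous section". The sentence ends there.
- Protocol v5.5, Appendix 2, Description of Statistical Methods: "All models will include trial centre, age at baseline, Gleason score, and PSA level at baseline (log-transformed) as covariates".

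The 10-year SAP, section 6.3, has nearly the same sentence as the 15-year SAP but continues: "and the baseline measure of the patient reported outcome being considered".

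Baseline data exist. Section 2.9.2 of the 15-year SAP says the measures were "completed at recruitment, at first biopsy, six months after randomisation, and yearly thereafter". Protocol 12.1 B places ICSmaleSF, ICIQ, SF-12, HADS and EQ-5D in the recruitment questionnaire. Protocol 13.5 describes the biopsy questionnaire as "containing similar measures used in the PCC clinic questionnaire (MTQ1) with the addition of the UCLA" EPIC index. Section 5.3 of the 15-year SAP also displays the baseline: "summary statistics by allocated group will be presented graphically for the baseline, 6-month, 12-month and subsequent assessment points up to 12 years". It is therefore plotted by arm but not used in the model.

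Three other passages bear on the point. The introduction to the 15-year SAP says: "As far as possible this plan will follow the approaches in the main ProtecT statistical analysis plan". Protocol Appendix 2, under Secondary analyses, provides for adding covariates where the arms are majorly imbalanced at baseline. Section 3.2 of the 15-year SAP keeps in each analysis every man with at least one post-randomisation measure.

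**The concern.** The score a man gave before treatment is a natural covariate for his later score on the same instrument. Randomisation was stratified by centre and minimised on age, Gleason score and PSA, so balance on baseline PROM scores rests on chance. If the baseline score predicts the score at 7 to 12 years, leaving it out of the model widens the interval for every arm comparison over months 73 to 144. It also leaves part of any chance baseline difference in the estimate. The trial already holds the data, and neither current text gives a reason for leaving the term out or says that baseline enters in another way, for instance as part of the outcome vector.

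**Working it through.** The documents give no standard deviation, target difference, power or baseline-to-follow-up correlation for any PROM, so there is no PROM figure of the plan to reproduce. The check has two parts.

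**1. Which instruments have a baseline?** The Appendix to the 15-year SAP lists seven instruments. Six have a documented pre-randomisation collection: ICIQ, ICSmaleSF, SF-12, HADS and EQ-5D at recruitment, and EPIC at biopsy. The seventh, EORTC QLQ-C30, is doubtful, because the summary of protocol changes for version 2.4 records "Addition of the EORTC QLQ-C30 questionnaire at 2 and 5 years' follow-up". EPIC may be missing for early entrants: it replaced FACT-P in 2003, while recruitment began in 2001.

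**2. What does omission cost for a continuous PROM?**

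Inputs: 545 men allocated to active monitoring and 553 to surgery (Protocol Appendix 2, The Number of Participants). The correlation r between baseline and follow-up score is an **assumption**, taken over 0.2 to 0.6. It should be read as what remains after centre, age, Gleason score and PSA are in the model.

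- Variance factor with adjustment, single visit: 1 − r².
- Equivalent sample-size inflation from omission: 1 / (1 − r²).
- Standard error without adjustment relative to with it: 1 / √(1 − r²).
- SE of a chance baseline difference: √(1/545 + 1/553) = 0.060 SD, so 95% of such differences lie within 1.96 × 0.060 = ±0.118 SD.
- Part of that difference carried into an unadjusted estimate: r × 0.118 SD.

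| r (assumed) | 1 − r² | Equivalent extra men | SE ratio | Carry-over, 95% range |
|---|---|---|---|---|
| 0.2 | 0.96 | 4% | 1.02 | ±0.024 SD |
| 0.3 | 0.91 | 10% | 1.05 | ±0.035 SD |
| 0.4 | 0.84 | 19% | 1.09 | ±0.047 SD |
| 0.5 | 0.75 | 33% | 1.15 | ±0.059 SD |
| 0.6 | 0.64 | 56% | 1.25 | ±0.071 SD |

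The last two columns are not separate losses. The carry-over is where the extra variance comes from, so they must not be added.

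To put this on the scale of power, take 545 men per arm with complete data and an assumed true difference of 0.15 SD. Power is about Φ(0.15 × √(545/2) / √(1 − r²) − 1.96). That gives 70% without the baseline, 74% at r = 0.3, 82% at r = 0.5 and 87% at r = 0.6.

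The planned test covers months 73 to 144, which is six annual assessments. For the mean of six visits with between-visit correlation c, the factor is 1 − r² / [(1 + 5c)/6]. With c = 0.6, a second assumption, the bracket is 0.667 and the factor is 0.94 at r = 0.2 and 0.46 at r = 0.6. The gain on the averaged outcome would then be larger than at one visit, but this rests on two unknown correlations. The single-visit range is the one to quote.

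**Binary PROMs.** The protocol plans two-level logistic models for these, and 1 − r² does not apply. An odds ratio is conditional on what the model contains, so leaving out a predictive covariate changes the odds ratio being estimated. The random intercept takes up some of the omitted variation between men, and the documents give no means of sizing the change.

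**The case against.** The strongest reply is that little is at risk. These are secondary outcomes in a randomised comparison that already adjusts for every stratification and minimisation variable. The unadjusted comparison of means is unbiased on average and its test is valid. A reader might infer that the estimates are biased or the tests unsound, and the documents do not support that.

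A reader might also infer that chance imbalance goes wholly uncorrected. It does not: Protocol Appendix 2 provides for adjustment where imbalance is major. That clause leaves smaller imbalances in place, does not define major, and yields no precision when the arms happen to be balanced.

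It can also be said that the adjustment was never withdrawn. The SAP introduction follows the 10-year plan as far as possible, and the protocol says the 10-year analyses will be repeated and offers its covariate list as a brief account. These are general statements. Both specific lists omit the term, and an analyst working from them would fit four covariates. The documents do not show whether the omission was deliberate, and a change between plans is no fault in itself. The point rests on the precision given up now.

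The size is open to challenge, and that challenge stands. No correlation is documented, and Protocol Appendix 2 describes the men as broadly healthy and without symptoms at entry. That suggests a narrow spread of baseline scores and possibly a low correlation.

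Finally, one might infer that the new estimates cannot be compared with the earlier ones. For linear models this is not shown, since the mean difference being estimated is the same with or without the covariate. The documents also show only the model planned for 10 years, not the one behind the published estimates.

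**Conclusion.** The point holds as one of efficiency. The 15-year PROM models omit a covariate that the trial collected before randomisation for most of its instruments, and the current documents give no reason. For continuous PROMs at a single visit, omission is like needing about 4% more men at r = 0.2 and 56% more at r = 0.6. That range is an assumption, and at 7 to 12 years the truth may lie near its lower end. For binary PROMs the consequence is a different odds ratio, of a size that cannot be stated. The primary outcome is untouched, and validity is not in question. The change is worth making because it costs almost nothing.

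**What to change.** In section 5.3 of the 15-year SAP and in Protocol Appendix 2 (Description of Statistical Methods):

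- Add to the covariates the baseline value of the PROM being analysed, wherever one exists. Define it as the last value before randomisation, since some instruments were completed both at recruitment and at biopsy.
- Keep men without a baseline value through a missing indicator or a mean-imputed baseline, so that every man with at least one post-randomisation measure stays in, as section 3.2 requires.
- Analyse instruments or cohorts with no baseline without the term, and list them. EORTC QLQ-C30 is the likely case, and early entrants may be another for EPIC.

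The cost is a few sentences, slightly more analysis work and an agreed rule for missing baselines. No new data are needed and no man is dropped.

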#### 5.4. Subgroup analyses

Following peer-reviewed criteria for the credibility of subgroup analyses (Sun et al, 2010), we have pre-specified a small number of subgroup analyses investigating whether treatment effectiveness in reducing prostate cancer specific mortality is modified by the following factors measured at diagnosis:

- Age (above versus below 65 years)
- Grade Group (Group 1 versus Group 2; Group 2 versus Group 3+)
- PSA (PSA < 10ng/ml versus 10 and above)
- Clinical stage (T1 versus T2)
- Aggregate tumour length in biopsy cores (<4mm versus 4mm+)
- Maximum tumour length in a single biopsy core (<2mm versus 2mm+)
- D'Amico low risk versus moderate / high risk.
- CAPRA low risk (score 0-1) versus moderate / high risk (>1)

Age, clinical stage, grade group, tumour burden and PSA are commonly used factors in the prediction of risk of disease progression. We anticipate that men at the lowest risk of disease progression have least to gain from radical treatment in comparison to their outcome with active monitoring. Wilt et al (2020) obtained results consistent with this hypothesis.

The D'Amico risk categories (D'Amico, 1998) are **low** (Gleason score is 6 or less, and PSA is 10ng/ml or less, and clinical stage is T1c/T2a); **high** (Gleason score is 8 or more, or PSA more than 20ng/ml, or stage is T2c); and **intermediate** (Gleason score is 7, or PSA is higher than 10ng/ml but no more than 20ng/ml, or stage is T2b).

To facilitate comparison of our results to those of Wilt et al (2020) we have adopted the CAPRA score of disease risk (Cooperberg et al, 2006) and will repeat this set of subgroup analyses with all-cause mortality as the outcome measure.

The statistical models used in the primary analysis will be extended to incorporate interaction terms, to test null hypotheses of no variation in treatment effect across subgroups. For sub-group analyses based on age, PSA, and tumour length measures, the interaction test will be based on the continuous measure, and departures from the assumption of a linear relationship will be investigated (and accommodated if necessary) by introducing polynomial terms. Significance testing will be conducted with the principles of the primary analysis being followed as closely as possible.

We will also investigate whether the relative impact of intervention on key PROMs (pad use, nocturia, erectile dysfunction , and bloody stools) is modified by age and the risk of disease progression at baseline, as incorporated for the clinical measures.

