| 10 ng/ml+                                          |                                                                                         |                    |                                  |                      |
| Clinical stage at diagnosis                        |                                                                                         |                    |                                  |                      |
| T1c                                                |                                                                                         |                    |                                  |                      |
| T2                                                 |                                                                                         |                    |                                  |                      |
| CAPRA risk score                                   |                                                                                         |                    |                                  |                      |
| Low risk (score 0-1)                               |                                                                                         |                    |                                  |                      |
| Medium / high risk (score >1)                      |                                                                                         |                    |                                  |                      |
| D'Amico risk group                                 |                                                                                         |                    |                                  |                      |
| Low                                                |                                                                                         |                    |                                  |                      |
| Intermediate / high                                |                                                                                         |                    |                                  |                      |

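### 15-year SAP section 5.4 tests the CAPRA and D'Amico interactions on two-level splits, although it tests age, PSA and tumour length as continuous measures; if effect modification is graded, this loses power

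*Supplement*

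**What the plan says.** Section 5.4 of the 15-year SAP (version 1.0, November 2020) lists eight baseline factors. It extends the primary Cox model with interaction terms "to test null hypotheses of no variation in treatment effect across subgroups".

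- **Age, PSA and the two tumour length measures.** Each has a cut-point in the list and in Table 2, but the cut is for display: "For sub-group analyses based on age, PSA, and tumour length measures, the interaction test will be based on the continuous measure". Polynomial terms are to be tried for departures from linearity.
- **CAPRA.** Listed as "CAPRA low risk (score 0-1) versus moderate / high risk (>1". Table 2 has two matching rows, the second being "Medium / high risk (score >1". CAPRA is not named in the continuous-measure sentence.
- **D'Amico.** Section 5.4 defines low, intermediate and high, but the comparison is "D'Amico low risk versus moderate / high risk", again two rows in Table 2.
- **Grade Group.** Three levels are kept: "Group 1 versus Group 2; Group 2 versus Group 3" and above.

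The expectation behind the subgroups is that "men at the lowest risk of disease progression have least to gain from radical treatment". CAPRA is included so that results can be compared with the extended follow-up of an earlier trial of surgery versus observation, and the subgroup set is repeated for all-cause mortality. No interaction effect size, power or CAPRA distribution is given.

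**The concern.** The SAP already separates how a factor is displayed (in groups) from how it is tested (on its own scale), but it does not apply this to the one composite numeric score on the list. Every man above 1 is treated as having the same risk, and likewise the intermediate and high D'Amico groups.

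This matters because events are few. Protocol version 5.5, Appendix 2, extrapolates to 34 prostate cancer deaths by the end of 2020 and considers 48, 60 and 72 as higher-rate scenarios. CAPRA and D'Amico combine the risk factors, so they bear most directly on the expectation that low-risk men gain least. If a real gradient were missed, readers could take the result as evidence that the relative effects do not depend on risk.

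**Working it through.** The plan states no power for any of these tests, so there is no figure to reproduce.

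**Inputs from the documents.** Allocation is 545 / 553 / 545 (protocol Appendix 2), so active monitoring is 545/1643 = 0.332 of men. Monitoring versus both radical arms then gives p(1−p) = 0.332 × 0.668 = 0.222. Deaths D are 34, or 48 to 72. The significance level is 5%.

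**Assumptions.** Scores run from 0 to 7; 20% to 60% of men score 0-1 (five distributions); the prostate cancer mortality hazard ratio is 1.0, 1.3 or 1.5 per point; effect modification is linear unless stated.

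**Formula.** The noncentrality of the score interaction test (1 df) is about

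λ = D × p(1−p) × Var(score among deaths) × (log HR ratio per point)².

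Cutting the score multiplies λ by ρ², the squared correlation among deaths between the score and the indicator of scoring above 1.

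**One case in full.** Take 33% of men at 0-1 and a mortality hazard ratio of 1.3 per point. Then 20% of deaths fall at 0-1, the SD among deaths is 1.85 (variance 3.42) and ρ² = 0.40. Let the HR ratio be 1.5 per point, so (ln 1.5)² = 0.164.

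- 34 deaths: λ = 34 × 0.222 × 3.42 × 0.164 ≈ 4.2, power 54%. After the cut, 0.40 × 4.2 ≈ 1.7, power 26%.
- 72 deaths: λ ≈ 9.0, power 85%. After the cut, 3.6, power 48%.

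**Across the assumptions.** ρ² runs from 0.23 to 0.65. A score test with 80% power has λ = 7.85 on 1 df, or 9.63 on 2 df for three arms. At the low end, 0.23 × 7.85 = 1.81 gives 27%, and 0.23 × 9.63 = 2.22 gives 25%. At the high end the results are 61% and 60%. By share of men at 0-1:

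| Men scoring 0-1 | Power after cutting (80% for the score test, 1 df) |
|---|---|
| 45-60% | 47-61% |
| 33% | 38-50% |
| 20% | 27-42% |

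With three arms, the score test and the two-level test both use 2 df, so testing the score costs no extra degrees of freedom.

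**Second distribution.** Suppose 3, 27, 28, 19, 11, 6, 3, 2 and 1% of men score 0 to 8. The variance is 2.608, the covariance with the indicator 0.492, and the indicator variance 0.7 × 0.3 = 0.21. So ρ² = 0.492² / (2.608 × 0.21) = 0.44, and 80% power on 2 df becomes 44%. Weighting men by an assumed log hazard of 0.2 to 0.35 per point lowers ρ² to 0.36-0.30 and power to 37-31%.

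**Simulation of deaths, 50% of men at 0-1.**

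| Truth | 48 deaths: score v cut | 72 deaths: score v cut |
|---|---|---|
| Linear, log HR ratio 0.4 per point | 68% v 39% | 83% v 55% |
| Linear, 0.7 per point | 97% v 78% | 99.9% v 92% |
| Step between 1 and 2, log HR ratio 1.5 | 31% v 58% | 45% v 75% |

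**Steps elsewhere.** If the ideal test has 80% power and the true step is at 3 or more, or at 4 or more, the score test has 52-67% and the cut 12-45% over the assumed distributions. If the step lies exactly between 1 and 2, the cut has 80% and the score test 27-58%.

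No power was computed for D'Amico. The documents do not give its distribution, and the point there rests on the loss of the ordering.

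**The case against.** **The best form depends on an unknown shape.** Section 5.4 says that the lowest-risk men have least to gain. It does not state a gradient, and low versus the rest tests that sentence directly. Under a step at the 1/2 boundary the split wins clearly. This stands, and it means that the score test is not uniformly better. But the SAP does not claim a step there. The advantage reverses once the step moves to 3 or more, and the planned polynomial check would protect the score test against non-linearity, whereas nothing in the plan protects the split.

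**Comparability.** A named low-risk group helps comparison with the earlier trial. That stands as a reason to report rates in the two groups. It is not a reason to restrict the interaction test to them.

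**Low power either way.** At 34 deaths with modest modification both tests are weak; the full case above gives 54% v 26%. So the change would not make a null result conclusive.

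**Timing.** The summary of SAP changes says that the SAP was published before data access. Protocol section 3.1 says that a January 2022 meeting with the Trial Steering Committee confirmed that the median 15-year results underpin the need for further follow-up. A change for 15 years is therefore no longer prospective. This stands and limits the fix.

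**What a reader might wrongly infer about Grade Group.** One might conclude that Grade Group is also cut down, or that its two contrasts leave men out. The documents do not support that: three levels are kept in section 5.4 and Table 2, and the Table 2 footnote can be read as a single likelihood ratio test across all of them.

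**Conclusion.** The inconsistency is real and lies within one section: four factors are tested on their own scale, while a numeric score and an ordered three-level category are tested as two-level splits, with no reason given. If modification is linear in CAPRA, the split keeps roughly 25-65% of the information, and 80% power falls to about 25-61%. These figures rest on assumed score distributions, an assumed score range and assumed mortality gradients.

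It would be tempting to say that the split halves the power. That is one value inside the range. It needs a particular distribution and a mid-range starting power; the loss is smaller for strong interactions (97% to 78%), and the sign reverses for a step exactly at the 1/2 boundary. The supportable statement is the range with its conditions. The point concerns secondary effect-modification tests, so it is a cheap improvement and no threat to the main result.

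**What to change.** In section 5.4, add the CAPRA score to the factors whose interaction test uses the continuous measure, with the same polynomial check. For D'Amico, replace the two-level split in the test by one ordered term over low, intermediate and high. Apply both to the all-cause mortality repeat. Keep scores 0-1 versus above 1, and low versus moderate/high, in Table 2 for display and for comparison with the earlier trial. Grade Group needs no change on this account.

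Make the change prospectively for the 20-year analysis, which protocol Appendix 2 says will follow similar approaches to the 15-year one. At 15 years, report the score-based and ordered tests beside the pre-specified splits as a declared addition; section 1 of the SAP already requires amendments to be described and justified.

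The cost is a sentence or two and no new data. The downsides are a linearity assumption for CAPRA, which the polynomial check addresses, equal spacing of the D'Amico levels, and lower power if the truth is a step exactly between scores 1 and 2.
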